### Interventions

The development of the GSP and GHE interventions has been described in detail in previous publications [35,36]. Multimedia Appendix 2 shows a detailed description of the content of both interventions, which has also been previously published [37].

#### Group Support Psychotherapy Training

Over a 4-month period (January-April 2016), Makerere University in collaboration with the Ministry of Health designed a GSP training program that consists of both formal and informal training. Between May and August 2016, the training-of-trainers model was used to deliver the training, whereby mental health specialists trained PHC health workers who in turn trained the LHWs. Formal training consisted of 8 training modules delivered in a 5-day training workshop that employed active learning techniques including role plays, brainstorming sessions, and small group discussions.

In brief, the first three modules including an overview of the training program, introduction to the GSP model, and introduction to depression and HIV/AIDS were delivered on the first day. On the second and third days, modules on basic counseling skills and effective coping strategies were delivered, respectively. On the fourth day, participants received training in basic livelihood skills (enterprise selection, basic financial skills, and resource mobilization) required to overcome poverty. The last day of training focused on self-care strategies, post-training assessments, and training workshop evaluation. Informal training consisted of conducting supervised pilot GSP sessions. Multimedia Appendix 3 summarizes the competencies targeted by the training.

#### Group HIV Education Training

In May 2016, Makerere University in collaboration with The AIDS Support Organization (TASO), designed a group HIV education training program that consisted of both formal and informal training. Between May and August 2016, the training-of-trainers model was used to deliver the training, whereby TASO HIV care providers trained PHC health workers who in turn trained the LHWs. Formal training consisted of five training modules delivered in a lecture format in a 2-day training workshop. In brief, on the first day, three modules including an overview of the training program, introduction to depression and HIV/AIDS, HIV progression and transmission were delivered. On the second day, modules on mother-to-child transmission and basic facts on ART were delivered. Informal training consisted of conducting supervised pilot GHE sessions.

#### Intervention Fidelity

Between September and December 2016, trained LHWs delivered the interventions to PLWH with mild to moderate depression recruited to participate in the trial. Strategies to ensure treatment fidelity in both treatment arms included the use of standardized intervention materials, structured health worker training, ongoing supervision, and training a larger number of LHWs than was required in order to avoid potential disruptions due to illness or job transfers. The LHWs underwent standardized training by trained primary care health workers. Each LHW delivered GSP or GHE following a manual translated into the local language. Prior to the sessions, each LHW drew up a schedule indicating which day of the week each group session would take place and handed it over to their supervisor. Of the 8 sessions to be delivered, 3-4 sessions were supervised by a trained PHC worker who assessed the LHW’s basic counseling skills using a supervision checklist with items adapted from the Enhancing Assessment of Common Therapeutic Factors scale [38].

In addition, the LHWs who facilitated group sessions were required to complete a self-administered semistructured feedback questionnaire after each group session in which they described content delivered in each group session and provided feedback on facilitators and barriers faced during the group session. Their feedback was discussed with their supervisors who advised on how to address any difficult issues raised. From this feedback, supervisors were able to assess whether the intervention delivery progressed as planned or not and to intervene accordingly.

### Participant Safety

During baseline assessments, participants were carefully screened and individuals for whom the interventions were deemed medically inappropriate or unsafe were excluded. Outcome assessors screened all participants for adverse events at the end of treatment and at 6 months after the end of the intervention using a standard interview and reporting form. Going forward, follow-up assessments will continue at 6-month intervals up to 2 years after the end of treatment. Any unfavorable and unintended sign or symptom associated with the participation in either intervention, regardless of whether it is considered related to the therapy is reviewed by the investigating team for seriousness, study relatedness, and expectedness. Similar information reported by participants at other times (eg, during intervention encounters) is duly noted and followed up with, as needed, to assure participant safety. Adverse events are reported according to the data and safety monitoring plan shown in Multimedia Appendix 4.

### Retention

Currently, trial participants have received their 6-month outcome assessment and will be due for their 12-month outcome assessment in January-February 2018. In order to maximize adherence and retention, we formed community advisory boards to monitor community satisfaction with implementation activities and to provide feedback to investigators in real time on any conflicts or dissatisfaction arising from project implementation activities. Lay health workers who facilitated the group sessions and the primary care health workers who supervised them were provided with a financial incentive as an appreciation of their commitment to the project. For participants who missed group sessions, the LHWs made home visits to re-engage them. Given that group sessions took place in the villages, the LHWs know the homes of the participants and have been able to mobilize them to return for their follow-up assessments.

### Study Measures and Data Collection Schedule

So far, assessments of study measures have been conducted at baseline, at the end of the interventions (2 months), and 6 months after the interventions. Going forward, further assessments will be conducted at 12, 18, and 24 months after the intervention. Table 1 [32,34,39-47] summarizes the study measures including the primary and secondary outcomes, process evaluation outcomes, potential effect modifiers, and mediators.

**Table 1 table1:** List of study measures and data collection schedule.

Study measures		Instrument	Data collection schedule (months)					
			0	2	6	12	18	24
**Primary outcomes**								
	Major depression	The Mini International Neuropsychiatric Interview [32]	✓		✓	✓	✓	✓
	Functioning level	5-item locally developed function assessment method [39]	✓		✓	✓	✓	✓
**Secondary outcomes**								
	Depression symptoms	Self-Reporting Questionnaire [34]	✓		✓	✓	✓	✓
	Posttraumatic stress symptoms	Locally adapted Harvard Trauma Questionnaire [40]	✓		✓	✓	✓	✓
	Alcohol use	10-item Alcohol Use Disorders Identification Test [44]	✓		✓	✓	✓	✓
	Disability days	Single question “How many working days have you lost due to depression-related symptoms in the previous 30 days?	✓		✓	✓	✓	✓
	Cost-effectiveness	Estimation of incremental costs of the GSP intervention arm as compared to the control arm	✓		✓			✓
	Poverty index scores	Questions on indicators of socioeconomic status such as the building materials of the household dwelling unit, access to electricity, type of cooking fuel, source of lighting, household remoteness (distance to nearest health facility), household food security, household durable assets such as radios, televisions, and mobile phones	✓		✓			✓
	Adherence to ART	One question: “During the past week, on how many days have you missed taking all your medication doses?”	✓		✓	✓	✓	✓
	Viral load	Medical charts of study participants	✓		✓		✓	

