Secondarily, we aimed to compare the effects of GSP and GHE delivered by trained LHWs to PLWH presenting with mild to moderate depression in primary care on measures of self-esteem, posttraumatic stress symptoms, social support, stigma, adherence to ART, viral load, number of disability days, asset possession, poverty indices, and cost-effectiveness measures. We hypothesized that compared with PLWH receiving GHE, those receiving GSP will achieve a greater increase in social support and positive coping skills and greater reduction in stigma; larger increases in adherence to ART and greater reduction in viral load; and greater reduction in number of disability days, greater increase in asset possession scores, and larger reductions in poverty index scores at 6, 12, 18, and 24 months after the end of treatment.

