#### Participant Eligibility Criteria, Recruitment, and Masking

To be eligible for the study, PLWH had to be 19 years and older, diagnosed with major depression assessed with the MINI depression module [32], antidepressant naïve, using ART, and residing in the villages where the trained LHWs lived. Individuals with high suicide risk [33], a severe medical disorder such as pneumonia or active tuberculosis, psychotic symptoms, and hearing or visual impairment were excluded from the study.

On a given clinic day, project research assistants worked with primary care health workers of a participating PHC in the center’s HIV clinic. The primary care health worker gave a health talk on depression to clients in the waiting area. Clients who felt that they had experienced symptoms of depression described in the health talk were invited for further evaluations using the Luo version of the 20-item self-reporting questionnaire [34] and the MINI depression module. This procedure was repeated until a total of 40 PLWH diagnosed with major depression were obtained from a given PHC.

Clients diagnosed with major depression were approached by research assistants who explained study procedures, determined eligibility, and then obtained informed consent. Each client who gave informed consent received baseline assessments with a standardized questionnaire. Recruited participants from the same village were assigned to a trained LHW residing in or near their village to receive the intervention they had been trained to deliver (ie, either GSP or GHE).

By design, both experimental and control interventions were identifiable to participants but will be masked to outcome assessors, the Data and Safety Monitoring Board, and data analysts.

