### Statistical Analyses

We will assess randomization across the two arms by comparing sociodemographic characteristics and other potential confounding variables using chi-square for categorical variables, and *t* tests or other equivalent nonparametric tests, as appropriate, for continuous variables. Primary outcomes will be the difference in follow-up proportions of participants who meet MINI criteria for major depression and difference in follow-up function scores of participants in the intervention and control arms 6 months after the end of treatment.

Secondary outcomes will include measures of self-esteem, posttraumatic stress symptoms, social support, stigma, alcohol use, ART adherence, viral load, number of disability days, asset possession indices, and cost-effectiveness data. Primary outcomes, secondary outcomes, and all subgroup analyses will be analyzed by ITT using a multilevel mixed model adjusting for clustering in health centers to determine effect modifiers [49]. The status of randomization (intervention/control) and baseline depression score will be included as a covariate. To account for the clustered design, we will treat clusters as a random effect. Potential confounding variables (eg, age, gender, socioeconomic status) with significant differences across intervention and control arms will be included as fixed factors. The R statistical software will be used to conduct all analyses [50]. A process evaluation using mixed methods to assess acceptability, feasibility, fidelity, causal mediating processes, and contextual influences in the trial will be conducted.

The primary analysis will follow ITT principles and use all available follow-up data, with missing data handled directly through maximum likelihood estimation in mixed modeling. We will document the extent and pattern of missing data and the reasons and will conduct sensitivity analyses of the impact of missing data on stability of the primary results. Missing values will be imputed with multiple imputations. We will verify that mixed model‒based results are not sensitive to violations of model assumptions with permutation tests.

Last, Cohen *d* effect sizes will be computed for the effect estimates to determine the size of the intervention effect [51].

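### The poverty index includes remoteness, which GSP should not move, and the stated model names no baseline poverty adjustment: a possible loss of precision on one secondary outcome

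*Protocol article*

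**What the plan says.** Table 1 of the protocol article lists the poverty index among the secondary outcomes, measured at 0, 6 and 24 months. Its indicators cover dwelling materials, electricity, cooking fuel, lighting, and "household remoteness (distance to nearest health facility), household food security, household durable assets". The list is open-ended, and no weights or scoring rule are given.

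The Introduction states the hypothesis for GSP as "larger reductions in poverty index scores at 6, 12, 18, and 24 months after the end of treatment". The livelihood content that might produce this is described under Group Support Psychotherapy Training: "participants received training in basic livelihood skills (enterprise selection, basic financial skills, and resource mobilization) required to overcome poverty".

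Under Participant Eligibility Criteria, Recruitment, and Masking, participants had to be "residing in the villages where the trained LHWs lived". The cluster eligibility criteria in turn require those lay health workers to live in villages that the health center serves.

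Statistical Analyses sets one model for all outcomes, "analyzed by ITT using a multilevel mixed model adjusting for clustering in health centers to determine effect modifiers", with centers as a random effect. On covariates it says: "The status of randomization (intervention/control) and baseline depression score will be included as a covariate". Age, gender, socioeconomic status and similar variables enter only where the arms differ significantly.

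**The concern.** Distance to a health facility is a plausible marker of poverty, but training in enterprise, finance and resource mobilization has no evident route to shortening it. The item therefore brings variance to the outcome and almost no treatment signal. Recruitment by village makes it likely that much of this variance lies between health centers, the randomized units. With 15 centers per arm, between-center variance is the costly kind, because recruiting more people within a center does not average it away.

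The usual remedy is to adjust for the outcome's own baseline value, which Table 1 shows is collected. The covariate rule names baseline depression score for every outcome and leaves socioeconomic status to a significance test between arms. That test answers the wrong question: a prognostic baseline value improves precision whether or not the arms happen to differ on it. At stake is the chance of detecting a real economic gain on this index.

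**Working it through.** **The plan's own figure.** The article gives no power or variance figure for the poverty index. Its power figure is for major depression. With 25% vs 15%, k = 0.25, 32 per cluster and two-sided 5%: (1.96 + 0.8416)² × [0.1875/32 + 0.1275/32 + 0.0625 × (0.0625 + 0.0225)] / 0.10² = 7.849 × 1.5156 = 11.9, so 12 clusters per arm, with power 0.803. This matches Table 2 but has no bearing on this point.

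**Inputs from the article.** c = 15 centers per arm; m = 32 analyzed per center (40 less 20% loss); seven listed domains, one of them remoteness.

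**Assumptions, not in the article.**
- Equal weights and unit-variance items.
- ICC 0.05 for the six other items, with correlation ρ between them of 0 or 0.3.
- Remoteness constant over time, unrelated to the other six, with ICC 0.1 to 0.5.
- Within-center baseline-to-follow-up correlation of 0.7 for the six-item score, with its center component stable over time.

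**Comparison of follow-up scores without the baseline index.** SE = √[2(V_b + V_w/m)/c], where V_b and V_w are the between- and within-center variances. The six-item sum has variance 6 + 30ρ.
- ρ = 0, without remoteness: V_b = 0.30, V_w = 5.70, SE = √[2(0.30 + 0.178)/15] = 0.253.
- ρ = 0, with remoteness at ICC 0.5: V_b = 0.80, V_w = 6.20, SE = √[2(0.80 + 0.194)/15] = 0.364.

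| ρ | Remoteness ICC | SE without item | SE with item | Increase |
|---|---|---|---|---|
| 0 | 0.1 | 0.253 | 0.284 | 13% |
| 0 | 0.3 | 0.253 | 0.327 | 29% |
| 0 | 0.5 | 0.253 | 0.364 | 44% |
| 0.3 | 0.1 | 0.399 | 0.420 | 5% |
| 0.3 | 0.3 | 0.399 | 0.450 | 13% |
| 0.3 | 0.5 | 0.399 | 0.478 | 20% |

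**Change from baseline.** A constant item in an additive score is present at both visits and subtracts out. In simulation (2000 runs per setting) the SE was identical with and without it, for example 0.118 and 0.118 at ρ = 0, and 0.185 and 0.185 at ρ = 0.3.

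**Baseline index as covariate.** In the same simulation, using least-squares regression on individual data, the increase ran from about 0% (0.197 to 0.198) to 12% (0.120 to 0.134). A mixed model uses a slope nearer the within-center one. At the least favorable setting that slope is 0.70 without the item and (0.7 × 5.70 + 0.50)/6.20 = 0.724 with it. The SEs are then √[2(0.30² × 0.30 + 2.907/32)/15] = 0.125 and √[2(0.276² × 0.80 + 2.948/32)/15] = 0.143, a rise of about 14%. The 12% is therefore approximate, but the order of size holds.

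**Bias.** With no treatment effect, the mean simulated arm difference was about zero in every setting.

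**Which remedy does more.** At ρ = 0 and remoteness ICC 0.5, dropping the item alone brings the SE from 0.364 to 0.253. Keeping it and adjusting for the baseline index brings the SE to about 0.134 to 0.143.

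**The case against.** The strongest reply is that the article never says this outcome will be compared at follow-up without its baseline. The Introduction predicts reductions, and the follow-up wording in Statistical Analyses defines only the two primary outcomes. An analysis of change would remove the problem. This stands, and it makes the point conditional. It does not remove the point, because the one covariate rule the article states names baseline depression score and not the baseline poverty index.

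Second, weights and scoring may be fixed in a fuller document, and their absence from an article is no fault. That also stands. The percentages are illustrations under assumed weights. A reader might infer a larger penalty: with independent items, ICC 0.03 for the other six and about 30 analyzed per center, remoteness at ICC 0.5 would raise the SE by 55%. That figure needs every other item to cluster weakly, although electricity supply may also be a village property. With the others at ICC 0.10 and remoteness at 0.3, the rise is 19%.

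Third, a reader might infer that a chance difference in remoteness biases the comparison. The documents do not support that. Centers were randomized, and the random center effect carries between-center variation into the standard error. Socioeconomic status is also a named example of what would be added if the arms differed significantly, so a marked imbalance could trigger adjustment.

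Fourth, asset possession is listed as a secondary outcome with its own hypothesis, so the economic question does not rest on this index alone. Finally, remoteness is not strictly fixed: households move, facilities open, and distance varies within a village. Both points stand and reduce the weight of the concern.

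**Conclusion.** The point holds in a limited form. The index contains an item that GSP would not be expected to change and that probably clusters by center, and the stated covariate set does not protect against it. If follow-up scores are compared on that covariate set, the standard error is inflated by roughly 5% to 44%. The inflation is zero for an additive change score and about 0% to 12% with the baseline index as covariate. All three figures depend on the assumed weights, ICCs and correlations.

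It is a matter of precision on one secondary outcome. It does not touch the primary outcomes. It also does not show that remoteness must be removed from the outcome: the article defines the index with that item in it, and baseline adjustment recovers more precision than removal does.

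**What to change.** In the Statistical Analyses model for the poverty index, include the baseline poverty index as a covariate in every case, without waiting for a significant baseline difference. Baseline remoteness alone is an acceptable alternative for this item, but it leaves the baseline variation in the other items unused.

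Keep the full index as the defined outcome. Prespecify one sensitivity analysis with the index scored without the remoteness item at all visits.

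The cost is one extra covariate and one extra analysis, on data already scheduled for collection. The article reports that analysis of the 6-month data is in progress, so the change should be dated and should state whether the 6-month poverty comparison by arm had been seen. The same caution is a reason not to redefine the main score at this stage.

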**Potential effect modifiers**								
	Sociodemographic variables	Standardized Demographic Questionnaire	✓					
	Trauma events	Locally developed 16-item trauma event checklist	✓					
**Potential effect mediators**								
	Self-esteem	Rosenberg Self-Esteem Scale [41]	✓		✓	✓	✓	✓
	Social support	12-item Multi-Dimensional Perceived Social Support scale [42]	✓		✓	✓	✓	✓
	HIV-related stigma	HIV-related stigma scale [43]	✓		✓	✓	✓	✓
	Coping skills	COPE Inventory [45]	✓		✓	✓	✓	✓
	The therapeutic relationship	The Scale to Assess the Therapeutic Relationships–Patient version [46]		✓				
**Process evaluation outcomes**								
	Indicators of feasibility	The proportion of eligible participants who take up either intervention (Reach), the proportion who attended all 8 sessions of either intervention (dose delivered), and the proportion who are lost to follow-up (attrition) will be determined from the attendance registers		✓				
	Indicators of acceptability	A 9-item questionnaire [47] will assess participant’s satisfaction, the group facilitators’ knowledge and attitudes, and the participant evaluation of the intervention’s ability to reduce depression.			✓			
	Fidelity	A semistructured self-administered questionnaire completed by group facilitators will assess whether or not the interventions were delivered as planned.		✓				
	Contextual influences	A semistructured self-administered questionnaire completed by group facilitators will assess any facilitators or barriers to intervention delivery that they observed during group sessions.			✓			
	Causal mechanisms	A semistructured interviewer-administered questionnaire will assess participant’s knowledge, skills, or assets acquired during and after the interventions, which will give an indication as to whether or not the interventions influenced targeted risk factors for depression.			✓			

**Table 2 table2:** Sample size and power calculations.

Alpha	Beta	*k*	Cluster size	Control group proportion	Intervention group proportion	Minimum clusters required	Resulting power
.01	.2	.25	32	0.25	0.15	18	0.808
.05	.2	.25	32	0.25	0.15	12	0.803
.01	.2	.25	40	0.25	0.15	16	0.818
.05	.2	.25	40	0.25	0.15	11	0.823
.01	.2	.25	32	0.3	0.15	10	0.842
.05	.2	.25	32	0.3	0.15	7	0.849
.01	.2	.25	40	0.3	0.15	9	0.851
.05	.2	.25	40	0.3	0.15	6	0.84

